#### 2.3.4 Sample sizes

According to a previous study of peri-menopausal women in China (Zhang et al., 2014), we assumed that the mean ± standard deviation (SD) differences in the change in total KI score of the intervention group and the control group were 9 ± 7 and 3 ± 7. PASS 15 software was used for sample size calculation. We determined a sample size of 30 women for each group, with α equal to 0.05 (two-sided) and β equal to 0.01.

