## 2 Materials and methods

### 2.1 Study design

This is a multicenter, randomized, controlled trial to investigate the efficacy and safety of HHXYP by comparing with oryzanol. Sixty participants will be included from the following three hospitals: Tongji hospital, Tongji Medical College, Huazhong University of Science and Technology (HUST); Maternal and Child Hospital of Hubei Province, Tongji Medical College, HUST; Wuhan Maternal and Child Health Hospital, Tongji Medical College, HUST. Tongji Hospital is the central structure of the study.

The duration of this study is 17 weeks including screening period of 1 week, treatment period of 12 weeks, and follow-up period of 4 weeks. Informed consent form signed by all qualified participants before enrollment. The Ethics Committee of Tongji Medical College, Huazhong University of Science and Technology approved this trial (approval number:2021S188). The protocol design conformed to the Declaration of Helsinki (Version Edinburgh 2000) and registered on the Chinese Clinical Trial Registry (ChiCTR2100050783). The flow chart of the study has been presented in Figure 1.

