### 2.2 Randomization, allocation concealment and blinding

These participants will be randomly in a 1:1 ratio to HHXYP treatment group and OC group. An independent statistician will use SPSS software to generate the randomization sequence. The designated researcher in the central structure will prepare the assignments in opaque envelopes in sequence, and inform the researcher of the matching card number either by text message or *via* mobile communication application. To ensure blindness in this trial, both of HHXYP and oryzanol pills were packaged with the same appearance throughout the study process, outcome assessors and the data analysts will be blinded to the group allocation.

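### Thirty women per group gives about 90% power on the protocol's own inputs, not the 99% implied by β = 0.01

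*Protocol article*

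**What the plan says.** All the inputs are in section 2.3.4 of the protocol article. The assumed changes in total KI for "the intervention group and the control group were 9 ± 7 and 3 ± 7". The software is given as PASS 15, and the error rates and the result are stated together: "We determined a sample size of 30 women for each group, with α equal to 0.05 (two-sided) and β equal to 0.01".

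The rest of the article agrees with that result. Section 2.2 sets 1:1 allocation, and section 2.1 gives the total: "Sixty participants will be included from the following three hospitals". Sixty is exactly twice 30, so the planned total contains no visible margin for loss. Section 2.3.4 does not name the test behind the calculation, the visit at which the change is taken, or any correlation between repeated measurements.

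**The concern.** β = 0.01 means 99% power. A standardised difference of 6/7 = 0.857 is large, but 30 per group is the size one expects for about 90% power at that difference. The stated β and the stated sample size therefore looked incompatible.

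What is at stake is the design claim for the primary outcome. A reader, ethics committee or later meta-analyst is told that the trial has a 1 in 100 chance of missing a 6-point benefit. If the true figure is nearer 1 in 10, a non-significant result is weaker evidence against such a benefit than the article suggests. If 99% power was the real intention, the trial is too small.

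**Working it through.** **Inputs** (section 2.3.4 unless noted)

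- Difference in mean change: 9 − 3 = 6 points
- SD of the change: 7 in each group
- α = 0.05, two-sided; β = 0.01
- Allocation 1:1 (section 2.2)
- 30 per group, 60 in total (section 2.1)

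**Attempt to reproduce 30 per group at β = 0.01.** Normal approximation:

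n per group = 2 (z₀.₉₇₅ + z₁₋β)² × SD² / Δ²

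- β = 0.01: 2 × (1.960 + 2.326)² × 49/36 = 50.01, rounded up to 51
- β = 0.10: 2 × (1.960 + 1.282)² × 49/36 = 28.6, rounded up to 29

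The exact two-sample t-test (noncentral t, 2n − 2 degrees of freedom) gives:

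| β | Power | n per group, exact | Rounded up |
|---|---|---|---|
| 0.20 | 80% | 22.4 | 23 |
| 0.10 | 90% | 29.6 | **30** |
| 0.05 | 95% | 36.4 | 37 |
| 0.01 | 99% | 51.0 | **51** |

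The planned 30 is not reproduced at β = 0.01. It is reproduced exactly at β = 0.10.

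**Power at the planned size.** The noncentrality is Δ / (SD × √(2/n)) = 6 / (7 × √(2/30)) = 3.32. The normal approximation gives power Φ(3.32 − 1.96) = 0.913. The exact t-test gives 0.904, so β is about 0.096.

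**What 99% power at 30 per group would require.** Either a difference of about 7.9 points with SD 7 (power 0.990), or an SD of about 5.3 with a 6-point difference (power 0.991). Section 2.3.4 states neither.

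**Other readings tried**

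- One-sided α of 0.05 at 99% power: 43 (normal) or 44 (exact) per group. One-sided power at 30 per group is about 95%.
- α and β exchanged (α = 0.01, β = 0.05): 49 or 51 per group.
- Adjustment for baseline, treating 7 as the unadjusted SD: power at 30 per group is 0.983 with a correlation of 0.6 and 0.995 with 0.7. A correlation between these values would be needed, and none is stated.

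**Effect of loss.** The article gives no loss rate, so these rates are assumptions for illustration. With 10% loss (27 per group) exact power is 0.871. With 20% loss (24 per group) it is 0.828.

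**The case against.** The strongest objection is that this is a one-digit misprint. Because β = 0.10 returns exactly 30, the trial was probably planned at a conventional 90%, and no patient, analysis or decision rule changes. This is the likeliest explanation, and it determines the remedy. It does not make the printed figure right, and the figure is the article's only statement of power for its primary outcome.

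A second objection is that the test is unnamed and section 2.8 plans repeated-measures ANOVA. If the outcome were the mean of four post-baseline visits, each with SD 7, 30 per group would reach 99% power at a between-visit correlation of about 0.43: the SD of the mean would be 7 × √((1 + 3 × 0.43)/4) ≈ 5.3. That is arithmetically possible, but section 2.3.4 mentions neither averaging nor a correlation, and β = 0.10 explains the figure without further assumptions. The conclusion should therefore be read as applying to a two-group comparison of change, which is what the stated inputs describe.

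Third, an article may leave a dropout allowance to the full protocol. This is accepted: its absence is not counted as an error here, and the loss figures only show how power depends on complete data. It is also fair to say that the article does not itself use its power figure to interpret a null result; that risk lies with its readers.

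**Conclusion.** The concern holds. On the article's own inputs, β = 0.01 and 30 per group cannot both be right. Thirty per group gives 90.4% power (β about 0.096), and 99% power needs 51 per group, 21 more in each arm. This rests on a two-sample comparison of change in KI with SD 7, two-sided α of 0.05 and complete data. None of the tests or error rates tried gives 30 at 99% power without an additional correlation that the article does not state. The probable cause is a misprint of 0.10. The document alone cannot prove which figure was entered in PASS.

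**What to change.** Check the saved PASS 15 output and correct section 2.3.4. If it confirms β = 0.10, the text could read: 30 women per group give 90% power (β = 0.10) to detect a 6-point difference in change in total KI, with SD 7, two-sided α of 0.05 and complete data. Keep N = 60. Add one sentence giving the power under whatever loss the sponsor expects; for orientation, it is about 87% at 10% loss and 83% at 20%.

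This costs one figure and one sentence, with no extra patients and no change in conduct. The stated power becomes less favourable. Section 2.10 reports nine women enrolled by 1 June 2022, so as of that date the correction could be made well before results.

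If the output shows that 99% power was truly intended, the choice is between 51 per group (102 in total, 42 more than planned, before any loss) and stating openly that 60 women give about 90%. If the calculation relied on repeated measures or baseline adjustment, the assumed correlation must be stated.

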### 2.4 Interventions

#### 2.4.1 HongHua XiaoYao Pill group

Participants in HHXYP group will receive two HongHua XiaoYao pills (produced by Jiangxi Puzheng Pharmaceutical Co., Ltd. China, specification: 0.39g/pill) three times daily for 12 weeks.

#### 2.4.2 Oryzanol control group

Participants in OC group will receive two Oryzanol pills (produced by First Pharmaceutical Factory of Hainan Pharmaceutical Co., Ltd. China, specifications: 10mg/pill) three times daily for 12 weeks.

### 2.5 Outcomes

#### 2.5.1 Primary outcome

The primary outcome of the study is the modified Kupperman Index (KI), which will be measured at baseline and 4, 8, 12, 16 weeks after randomization. The total score of KI is 63. It includes 13 items related to peri-menopausal syndrome, and the severity score of each item ranges from 0 to 3. There were different basic score in each item: hot flashes and sweating = 4; Paresthesia, sleep disorders, nervousness, sexual complaints, urinary tract infection = 2; the other items = 1. Item score = basic score × severity score. Classification standard of disease condition: mild: symptom score <13; moderate: symptom score 14–26; severe: symptom score >27 points.

#### 2.5.2 Secondary outcomes

The secondary outcomes include the following items:

##### 2.5.2.1 Hot flash scale

The average frequency and severity of hot flash per week will be recorded by participants from baseline (-1 week) to week 16. The severity of hot flash was evaluated using visual analog scale (0–10). It also calculated baseline and 4, 8, 12, 16 weeks after randomization respectively.

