## Abstract

**Background:** Peri-menopausal syndrome (PMPS) has a high incidence rate and seriously affects the physical and mental health of women. Honghua Xiaoyao Pill (HHXYP) is a Chinese patent medicine, which has been reported to be used to treat PMPS. However, there is still a lack of randomized clinical trial to evaluate the efficacy and safety of HHXYP on life quality, mood and vasomotor symptoms for PMPS women. This study aims to investigate whether HHXYP is effective and safe in treating PMPS and the possible mechanism.

**Methods:** A multicenter, randomized, controlled clinical trial will be conducted in China to evaluate the efficacy and safety of HHXYP. Sixty women with peri-menopausal syndrome will be recruited at three centers and randomly in a 1:1 ratio to a treatment group using HHXYP (HHXYP group) and a control group using oryzanol (OC group). Participants will be treated with HHXYP or oryzanol for 12 weeks and followed up for 4 weeks. The primary outcome is the modified Kupperman Index (KI), which will be measured at baseline and 4, 8, 12, 16 weeks after randomization. The secondary outcomes include Hot flash scale (HFs), Menopause-Specific Quality of Life Scale (MENQOL) and Hamilton Depression/Anxiety Scale (HAMD/HAMA). The HFs are measured at the same point as the KI, other secondary outcomes are measured at baseline and 12, 16 weeks after randomization. The other outcomes are the levels of serum sex hormone, monoamine neurotransmitter, vascular vasomotor factor and the expression of phosphatidylinositol 3-active enzyme (PI3K)/protein activator enzyme B (Akt), which will be measured at baseline and 12 weeks after randomization. Adverse events will also be reported.

**Discussion:** HHXYP is a potential alternative Chinese patent medicine for PMPS. This trial will provide evidence for HHXYP on improving the quality of life, mood and vasomotor symptoms, and sex hormone levels of PMPS patients.

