### 2.7 Safety outcomes

In order to exclude serious heart, liver, and kidney diseases, all participants will also receive urine, stool, blood routine, liver function (ALT, AST), kidney function (BUN, creatinine) and ECG examination before and after treatment. Participants will inform the researchers adverse events or uncomfortable symptoms by WeChat software, telephone, or short message. Adverse events should be recorded in the Case Report Form and resolved immediately. Serious adverse events should be reported immediately to the principal investigator. The details of outcome assessment chart is given in Table 1.

**TABLE 1 T1:** Trial processes chart.

Period	Enrollment	Baseline	Treatment			Follow-up
Time points	Week -1	Week 0	Week 4	Week 8	Week 12	Week 16
Patients						
Medical history	√					
Physical examination	√				√	
Laboratory examination	√				√	
Informed consent	√					
Randomization	√					
Intervention						
HongHua XiaoYao Pills (HHXYP) group			0.39g/pill, 2 pills, three times daily			
Oryzanol Control (OC) group			10mg/pill, 2 pills, three times daily			
Outcomes						
the modified Kupperman Index (KI)	√	√	√	√	√	√
Hot flash scale (HFs)	√	√	√	√	√	√
MENQOL		√			√	√
HAMD		√			√	√
HAMA		√			√	√
Serum E2, FSH and LH levels		√			√	
Serum NE, 5-HT and DA levels		√			√	
Serum NO, ET-1 and CGRP levels		√			√	
Expression of PI3K, Akt, and pAkt		√			√	
Trial evaluation						
Safety of medicine			√	√	√	√
Adverse event			√	√	√	√
Reasons of drop-outs or withdrawals			√	√	√	
Patient’s compliance					√	

E2, estradiol; FSH, follicle-stimulating hormone; LH, luteinizing hormone; NO, nitric oxide; ET-1, endothelin-1; CGRP, calcitonin gene-related peptide; NE, norepinephrine; 5-HT, serotonin; DA, dopamine; PI3K, phosphatidylinositol 3-active enzyme; Akt, protein activator enzyme B; pAkt, phosphorylated protein kinase B.

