### 2.8 Statistical analysis

All data will be statistically analyzed using SPSS 20.0 software by a special analysts who is blinded to this trial. Continuous variables with normal distribution are presented as mean ± standard deviation (SD), and categorical variables are presented as frequency/percentage. All of the analyses will be performed on intention-to-treat (ITT) principle. Pearson’s chi-squared test or Fisher’s exact test are used to compare the frequency of categorical variables. Non-parametric Mann-Whitney test or Kruskal–Wallis test is used to compare data sets involving non-normal distribution. The comparison of continuous variables between groups will be evaluated by variance analysis. The main outcome scales at different time points will be analyzed by repeated measurement analysis of variance (ANOVA). Significance level is set as *p*-value less than 0.05.

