). Xiaoyao pills also has anti-inflammatory effect, which may relieve depression symptoms by inhibiting inflammatory reaction or activating NGF/BDNF-TRKA/TrkB-CREB pathway (Fang et al., 2020). On the other hand, Xiaoyao pills could reduce the level of inflammatory cytokines, enhance the expression of neurotrophic factors and synaptophysin to inhibite the behavior abnormality of LPS-induced depression-like model rats (Shi et al., 2019). Furthermore, Xiaoyao pills has antioxidant and neuroprotective effects on both cortical and hippocampal regions, which can improve depression-like behavior and oxidative stress of olfactory bulb excised rats by activating PIK3CA-AKT1-NFE2L2 BDNF signaling pathway (Ji et al., 2021). Therefore, it is reasonable to speculate that HHXYP has the effects of regulating anxiety and depression, anti-inflammation, and anti-oxidative stress. HHXYP has been reported as a complementary and alternative therapy for the treatment of gynecological diseases such as irregular menstruation, polycystic ovary syndrome and mastitis (Li 2014; Yan et al., 2020). There are also some researches indicated that it could alleviate peri-menopausal depression, insomnia and other peri-menopausal symptoms. HHXYP combined with estradiol tablets/estradiol dextroprogesterone tablets significantly reduced the modified KI, MENQOL score and serum FSH, LH levels, but increased serum E2 levels compare with estradiol tablets/estradiol dextroprogesterone tablets alone (Hai et al., 2021). HHXYP combined with Wenjing Decoction effectively improved the ovarian function and insomnia in patients with peri-menopausal syndrome compare with HHXYP alone (Zhang et al., 2015). HHXYP combined with conventional treatment (psychotherapy, vitamin D supplementation, HRT) improved Kupperman score and E2 levels compare with conventional treatment (Li et al., 2015). Based on the clues of clinical application and the theory of TCM, HHXYP seems show potential for treating PMPS. However, randomized controlled trials are still needed to determine. Therefore, this study will evaluate the efficacy of HHXYP for hot flash reduction, emotion improvement, and QOL improvement in PMPS patients. In order to better recruit participants, we set the age range between 45–60, as according to some reports, peri-menopause generally occurs around the age of 50 years, with a range between 40 and 60 years worldwide (Li et al., 2016).

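### Hot-flash averages are recorded every week, but the outcome is fixed at baseline and weeks 4, 8, 12 and 16 with no stated use of the weeks between

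*Protocol article*

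**What the plan says.** Section 2.5.2.1 sets up a weekly diary: "The average frequency and severity of hot flash per week will be recorded by participants from baseline (-1 week) to week 16". Severity is a 0–10 visual analog score. The next statement gives the time points of the outcome: "It also calculated baseline and 4, 8, 12, 16 weeks after randomization respectively".

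Two other places point to an outcome tied to visits. The Abstract says "The HFs are measured at the same point as the KI", and the KI is taken at baseline and weeks 4, 8, 12 and 16 (section 2.5.1). Table 1 ticks the hot flash scale in the visit columns only, but at six points, because both Week -1 and Week 0 are ticked.

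Section 2.8 names repeated-measures ANOVA for the main outcome scales and ordinary analysis of variance for other continuous comparisons. It has no rule for the diary and mentions no adjustment for baseline. Hot flashes are a secondary outcome, but the Discussion lists them first among the effects to be studied: "this study will evaluate the efficacy of HHXYP for hot flash reduction".

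**The concern.** The data are collected weekly, while the outcome is placed at visits four weeks apart. Nothing says what happens to weeks 1–3, 5–7, 9–11 and 13–15. If the value at a visit is that one week's average, three things follow.

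- Each value carries the full week-to-week variation of one diary week, although three further weeks are on file.
- A missed diary week at a visit leaves that time point empty, even when the neighbouring weeks were completed. If the hot flash scale falls under the repeated-measures ANOVA, the classical form of that analysis drops a woman who lacks any time point.
- The trial has 30 women per group, sized on the KI alone. Precision for hot flashes therefore has to come from how the diary is used.

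Even if averaging is intended, two analysts could derive different values from the same diary. They could also differ on whether Week -1 or Week 0 is the baseline.

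**Working it through.** **The plan's own figure.** The protocol gives no precision or power figure for hot flashes. Its only calculation (section 2.3.4) is for the KI: changes of 9 and 3, SD 7, two-sided α 0.05, β 0.01, 30 per group. Those inputs give n = 2 × (1.960 + 2.326)² × 7² / 6² ≈ 50.01, so 51 per group. The figure of 30 corresponds to β 0.10 (29 by the normal formula, 30 by the t test). That is a separate matter and does not enter below.

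**Count of records.** One pre-treatment week plus 16 weeks makes 17 weekly records. Five single-week values (baseline, weeks 4, 8, 12, 16) leave 17 − 5 = 12 unused, or 71%. This holds only if each value is one week. With averaging since the last visit, none is unused.

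**Assumptions for precision.** The documents give no week-to-week correlation r. I assume r is the same for every pair of weeks including the baseline week, weekly variances are equal, the effect is stable within the window, and r lies between 0.5 and 0.9.

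**One visit: mean of four weeks against one week.**

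- Unadjusted variance ratio: (1 + 3r)/4.
- With both analyses adjusted for one baseline week: [(1 + 3r)/4 − r²] / (1 − r²).
- The cut in the standard error is 1 minus the square root of the ratio.

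| r | Unadjusted ratio | SE cut | Adjusted ratio | SE cut |
|---|---|---|---|---|
| 0.5 | 0.625 | 21% | 0.375/0.750 = 0.500 | 29% |
| 0.6 | 0.700 | 16% | 0.340/0.640 = 0.531 | 27% |
| 0.7 | 0.775 | 12% | 0.285/0.510 = 0.559 | 25% |
| 0.8 | 0.850 | 8% | 0.210/0.360 = 0.583 | 24% |
| 0.9 | 0.925 | 4% | 0.115/0.190 = 0.605 | 22% |

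If correlation instead decays with distance (first-order autoregressive, lag-1 correlation 0.7 to 0.95), the unadjusted cut is 18% to 3%.

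**Whole treatment period: weeks 1–12 against the three visits at weeks 4, 8 and 12.**

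- Unadjusted ratio: [(1 + 11r)/12] / [(1 + 2r)/3]. At r = 0.5 this is 0.542/0.667 = 0.8125, a cut of 10%. At r = 0.9 it is 0.908/0.933 = 0.973, a cut of 1%.
- Adjusted, subtracting r² from both variances: 0.292/0.417 = 0.70, a cut of 16%, at r = 0.5; and 0.0983/0.1233 = 0.797, a cut of 11%, at r = 0.9.

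**Illustration in terms of power.** With 30 per group, two-sided α 0.05 and an assumed single-week standardized effect of 0.5, power for one visit is 48% (noncentral t, unadjusted). With the four-week mean it is 67% at r = 0.5, 58% at r = 0.7 and 51% at r = 0.9. The effect of 0.5 is an assumption, not a figure from the protocol.

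**The case against.** The strongest reply is that the text never says the other weeks are dropped. A reader might infer that only five weekly values are ever computed and that most of the diary is discarded. The documents do not support that as fact. Section 2.5.2.1 says the measure is *also* calculated at the visits, which can mean summaries in addition to the diary. It gives no averaging window, so the week-4 value could be a mean over weeks 1–4. Table 1 ticks six points, so the count of five is not settled either. This stands, and the loss must be stated as conditional.

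Second, the article condenses a fuller protocol, and an analysis plan may exist. A diary window for a secondary outcome often sits there. Silence on the window would not be enough to raise the point. What supports it is that the article does fix the time points, ties them to the KI visits in the Abstract, and names visit-based analyses without baseline adjustment. A method that uses the weekly records and the baseline would improve on what is written.

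Third, an analysis that pools visits recovers some of the precision. This stands too: over the whole treatment period the unadjusted gain is only 10% to 1%.

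Fourth, a mean over weeks 9–12 is not the same quantity as the week-12 value, and matching the KI time points is a legitimate choice. That is a reason to report both, not a reason to leave the weekly records unused.

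**Conclusion.** The point holds as a minor, inexpensive improvement. The plan collects weekly hot-flash averages, fixes the outcome at baseline and four later visits, and states no use for the weeks between. On the natural single-week reading, up to about 12 of 17 records do not enter the analysis. The standard error at a visit is then larger than it need be: a four-week mean would cut it by 21% to 4% unadjusted, or 29% to 22% with baseline adjustment, for an assumed equal correlation of 0.5 to 0.9. For the whole treatment period the cut is 10% to 1%, or 16% to 11% adjusted. If the sponsor already averages since the last visit, this loss is nil and only the wording needs completing.

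The size depends on the single-week reading, an assumed correlation and a stable effect within each window. It concerns a secondary outcome for which no power was claimed and leaves the primary KI comparison untouched.

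**What to change.** In section 2.5.2.1, define the hot-flash value at weeks 4, 8, 12 and 16 as the mean of the available weekly records since the previous visit (weeks 1–4, 5–8, 9–12, 13–16). Name the Week -1 diary value as the single baseline, and align Table 1 with that. In section 2.8, compare groups on these means with adjustment for that baseline. Alternatively, fit all weekly records in one mixed model with the same adjustment. Report the week-12 value alongside.

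The cost is wording and analysis code only; no new data, visits or participants are needed. At the status date in section 2.10 nine women had been enrolled, and the analysts are to be blinded, so the rule can be set before results are known. The one downside is small: if the effect is still growing during weeks 9–12, the four-week mean lies slightly below the week-12 value, which is why both should be shown.
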